**Address:**

**PharmaPart AG**

**[name]**

**[name]**

**[name]**

**Switzerland**

**[contact]**

**[contact]**

**www.pharmapart.com**

This report is to be sent per Fax on the SAE Report Form provided by the CRO. The CRO immediately will notify the Study Manager and the Study Coordinating CRA. The investigator is required to document in full the course of the SAE and any therapy given, including any relevant findings / records in the report. The investigator will also inform the CRO of the relevant follow up information and the outcome of the SAE as soon as possible using the standard form.

For reported deaths, the investigator is required to supply the sponsor with any additional available information (e.g.: autopsy reports and terminal medical reports).

All AEs and SAEs after enrollment of the subject (as soon as the informed consent has been signed) must be documented.

### Expected adverse reactions

**Atorvastatin** is generally well-tolerated and side effects are rare. Minor side effects include constipation, [diarrhea](http://www.medicinenet.com/script/main/art.asp?ArticleKey=1900), fatigue, gas, pruritus, heartburn, and headache. Major side effects include [abdominal pain](http://www.medicinenet.com/script/main/art.asp?ArticleKey=1908) or cramps, blurred vision, [dizziness](http://www.medicinenet.com/script/main/art.asp?ArticleKey=8004), easy bruising or bleeding, itching, muscle pain or cramps, rash, and yellowing of the skin or eyes. [An](javascript:defwindow('An')) [apparent](javascript:defwindow('apparent')) hypersensitivity [syndrome](javascript:defwindow('syndrome')) has been reported rarely. Atorvastatin, like other inhibitors of HMG-CoA reductase, occasionally causes [myopathy](javascript:defwindow('myopathy')) manifested as [muscle](javascript:defwindow('muscle')) pain, [tenderness](javascript:defwindow('tenderness')) or [weakness](javascript:defwindow('weakness')). Myopathy sometimes takes the [form](javascript:defwindow('form')) of [rhabdomyolysis](javascript:defwindow('rhabdomyolysis')) with or without [acute](javascript:defwindow('acute')) [renal](javascript:defwindow('renal')) [failure](javascript:defwindow('failure')) [secondary](javascript:defwindow('secondary')) to myoglobinuria. The [risk](javascript:defwindow('risk')) of [myopathy](javascript:defwindow('myopathy')) is increased by high levels of HMG-CoA [reductase](javascript:defwindow('reductase')) [inhibitory](javascript:defwindow('inhibitory')) [activity](javascript:defwindow('activity')) in plasma. Laboratory abnormalities may include elevated bilirubin, alkaline phosphatase, [thyroid](javascript:defwindow('thyroid')) function abnormalities.

Marked persistent increases of [serum](javascript:defwindow('serum')) transaminases have been noted. About 5% of patients had elevations of CK levels of 3 or more times the normal [value](javascript:defwindow('value')) on one or more occasions. This was attributable to the noncardiac fraction of CK. Muscle [pain](javascript:defwindow('pain')) or [dysfunction](javascript:defwindow('dysfunction')) usually was not reported.

Recenty, data from a retrospective analysis (conducted using pooled data from 44 completed trials comprising 16,495 dyslipidemic patients treated with atorvastatin, placebo, and other statins) has been reported. Only 3% of atorvastatin-treated patients withdrew from studies due to treatment-associated adverse events, compared with 1% of those on placebo and 4% of those receiving other statins; the most frequently reported treatment-associated adverse events were related to the digestive system. Serious adverse events were rare and seldom led to withdrawal. Persistent elevations in hepatic transaminases to >3 times the upper limit of normal (ULN) were experienced by 0.5% of atorvastatin-treated patients. A persistent elevation in creatine phosphokinase (CPK) was observed in only 1 atorvastatin-treated patient and was not associated with myopathy. No cases of rhabdomyolysis or myopathy were reported.

**Interferon-beta-1b** 250 micro g (8 million International Units [MIU]) administered subcutaneously every other day can cause injection side reactions such as erythema, pain or swelling or “flu-like” symptoms such as fever, myalgia, chills, headache or arthralgia. Elevation of hepatic enzymes and lowered WBC-counts were also reported.

### Unexpected adverse reactions

Unexpected adverse drug reaction is defined as an adverse reaction whose nature and severity is not consistent with the applicable product information.

## Dose reduction of Atorvastatin or Interferon-beta-1b

If an adverse event occurs due to Atorvastatin or Interferon beta-1b administration, haematological, serum chemistry and CPK will be tested.

### Creatine phosphokinase (CPK):

- CPK elevated factor 3:
  - CPK-control in two weeks
- CPK elevated factor 5:
- Atorvastatin will be reduced from 40mg to 20mg, if the isoenzyme CPK-MB is normal and in the absence of clinical symptoms (e.g. muscle pain, cramps)
- CPK elevated factor 10:
- Atorvastatin will be stopped

After two weeks haematological, serum chemistry and CPK testing will be repeated, and in the absence of normalized values, the Atorvastatin dose will be reduced/stopped until normalization of values is reached.

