In the case of severe depression, suicidal ideation, or attempted suicide, study medication must be interrupted until the patient’s psychiatric condition has been fully evaluated. A psychiatrist should be consulted whenever necessary. Treatment may be resumed only after consultation with the sponsor.

A patient may be withdrawn from further **study medication** under the following circumstances:

1. Laboratory abnormality or serious/severe adverse event if dose modifications in case of toxicities don’t counteract the abnormality.
2. At the discretion of the treating physician.

The development of conditions which would have prevented a patient’s entry into the study according to the selection criteria is no reason *per se* for withdrawal. However, the withdrawal in such cases remains at the discretion of the treating physician; in these cases, consultation with the sponsor before such a decision is requested.

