### Blinding

This is a rater-blinded study. All patients and the treating physician will be aware whether Atorvastatin is added to the Interferon-beta-1b therapy or not.

Treatment will be administered by the “treating physician” (TP). He/she will acknowledge the treatment administered, he/she will be responsible for patient eligibility, for treatment of adverse events, and for safety examinations.

”Examining physicians” (EP) will be responsible for disability scoring (EDSS, MSFC). They will not be informed whether patients are receiving Atorvastatin or not. Results of scoring will be recorded in a separate sheet. The EP will not acknowledge the treatment groups. Safety issues and other questions should not be discussed between TP and EP. Patients and TP should be informed not to discuss any safety questions with the EP.

In addition, the MRI evaluations will be performed with readers blinded to the treatment group.

Unblinding of the evaluating physician or his/her staff should generally be avoided. Single case unblinding is allowed when the actual treatment must be revealed in order to influence urgent medical care.

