#### Creatine phosphokinase (CPK)

Total CPK, isoenzymes only if total CPK is more than twice the normal upper range.

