### Unscheduled Visits

There are 2 reasons for an unscheduled visit.

1. If during the center-initiated telephone call to the patient the patient believes that they are having a relapse or if a patient should call the study center with complaint of a relapse, then the patient will be instructed to come in for an unscheduled visit within 7 days.

- Physical examination with vital signs
- Relapse reporting
- EDSS
- Adverse Events

2. If during the treatment phase a patient complains of symptoms related to medication side effects that the Treating Physician thinks requires a visit, the patient will come for an unscheduled visit.

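### At CPK factor 5 to below 10, the protocol mandates no immediate atorvastatin step for a patient with muscle symptoms, while an asymptomatic patient with normal CPK-MB is reduced at once

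*Protocol*

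**What the plan says.** Section 8.6.1 sets three CPK tiers. At factor 3, CPK is repeated after two weeks and the dose is left alone. At factor 5, "Atorvastatin will be reduced from 40mg to 20mg, if the isoenzyme CPK-MB is normal and in the absence of clinical symptoms", with muscle pain and cramps given as examples of symptoms. At factor 10, atorvastatin is stopped without any condition. Tests are repeated after two weeks and, "in the absence of normalized values, the Atorvastatin dose will be reduced/stopped until normalization of values is reached".

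Other sections bear on the same patient:

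- **Section 7.1.3** lists grounds on which study medication may be withdrawn. One is "Laboratory abnormality or serious/severe adverse event if dose modifications in case of toxicities" do not correct the problem. The other is "At the discretion of the treating physician". Its closing paragraph says that developing a condition that would have barred entry does not in itself require withdrawal. It leaves that decision to the treating physician and asks for sponsor consultation beforehand.
- **Section 7.2.4** says of the treating physician that "he/she will be responsible for patient eligibility, for treatment of adverse events, and for safety examinations".
- **Section 10.2.4** provides an extra visit: "If during the treatment phase a patient complains of symptoms related to medication side effects that the Treating Physician thinks requires a visit".
- **Section 8.2.2** orders "isoenzymes only if total CPK is more than twice the normal upper range", so CPK-MB is already available at factor 5.

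**The concern.** The CPK rule guards against statin muscle toxicity, a risk that the atorvastatin arm carries and the control arm does not. Section 8.5.6 describes myopathy as appearing through muscle pain, tenderness or weakness, with rhabdomyolysis as a possible form. Muscle symptoms should therefore lead to firmer action at a given CPK. In Section 8.6.1 they instead remove the patient from the only dose step written below factor 10.

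What is at stake is up to two weeks at full dose in a patient with possible myopathy, and uneven handling across 8 centres. One site may read the condition as meaning that other patients stop. Another may read it as meaning that other patients are not reduced and are retested. The words allow both.

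**Working it through.** The protocol gives no figure to reproduce here, so the check is to list the cases and look for an action in each. The tiers carry no inequalities; I read them as 3 to below 5, 5 to below 10, and 10 or more.

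| CPK factor | CPK-MB | Symptoms | Immediate atorvastatin step in Section 8.6.1 |
| --- | --- | --- | --- |
| 3 to below 5 | any | any | none; CPK repeated in two weeks |
| 5 to below 10 | normal | absent | reduce 40 mg to 20 mg |
| 5 to below 10 | normal | present | none written |
| 5 to below 10 | raised | present | none written |
| 5 to below 10 | raised | absent | none written |
| 10 or more | any | any | stop |

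One of the four cases in the middle band has an immediate step. I then looked for a rule elsewhere that fills the two symptomatic cases:

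- **Two-week retest (8.6.1).** It acts later, only if values have not normalised, and does not choose between reducing and stopping.
- **Laboratory or adverse-event ground (7.1.3).** It is optional and presupposes that dose modification has failed. No immediate modification is written for these patients.
- **Physician's discretion (7.1.3, second ground and closing paragraph).** It permits withdrawal from the first day but requires nothing.
- **Drug-related adverse event (opening of 8.6).** It orders laboratory tests only.
- **Sections 7.2.4 and 10.2.4.** They assign responsibility and allow a visit; neither gives a dose action.
- **Section 8.6.2.** It covers transaminases and leucocytes. Its 3x and 5x transaminase steps carry no symptom condition.

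None mandates an immediate step. The gap also lies on a likely testing route. Table 1 schedules CPK at baseline, month 6 and month 12, and treatment ends at month 12. With baseline limited to below 3 times the upper normal limit (Section 15.2), month 6 is the one scheduled on-treatment result that can change dosing. Other results come from adverse-event testing, and a patient tested for muscle pain already fails the no-symptom condition.

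**Size.** Inputs: about 60 patients, half on atorvastatin (Section 7), and, from Section 8.5.6, "About 5% of patients had elevations of CK levels of 3 or more times the normal" value on at least one occasion.

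- Atorvastatin patients: 60 / 2 = 30.
- Expected with CK at 3 times normal or more, assuming that rate applies here: 30 × 0.05 = 1.5.
- The gap is a subset with no stated rate, so the expected number is between 0 and 1.5. It would reach 1 only if 1 / 1.5 = 67% of those patients fell between factor 5 and 10 with muscle symptoms.

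Section 8.5.6 says muscle pain or dysfunction was usually not reported with these rises. Its pooled analysis of 44 trials found one persistent CPK elevation on atorvastatin and no myopathy. Twelve earlier months on 40 mg (Section 7.2.2) also lower the number. Interferon myalgia (Section 8.5.6) would raise the share with symptoms.

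**The case against.** The strongest reply is that the protocol leaves nobody without protection. The treating physician may withdraw atorvastatin at once, without waiting for a dose modification to fail. The closing paragraph of Section 7.1.3 plausibly covers this patient too, because CPK of 3 times the upper limit or more is outside the entry range and myopathy is an exclusion. It leaves withdrawal to that physician and asks for sponsor consultation. The two-week rule is a backstop. Allowing the half dose only with normal CPK-MB and no symptoms most naturally means that half a dose is not considered enough otherwise.

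Much of this stands. A reader might infer that the protocol keeps symptomatic patients on 40 mg. It does not: nothing directs continuation, and stopping is allowed from the first day. What the reply does not supply is a mandated action. Discretion and probable intent leave the two readings open.

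A reader might also infer that raised CPK-MB alone marks a higher-risk patient whom the rule neglects. The documents do not show this. Section 8.5.6 attributes statin-related CK rises to the noncardiac fraction, so normal CPK-MB reads as a check on the source of the rise. Raised CPK-MB without symptoms also lacks a written step, but it points to work-up rather than to shown statin muscle risk.

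**Conclusion.** The point holds for patients at CPK factor 5 to below 10 with muscle symptoms. No immediate atorvastatin step is mandated for them, while the asymptomatic patient with normal CPK-MB at the same level is reduced at once. It is a missing branch in a safety rule, softened by physician discretion and the two-week retest.

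Severity is minor. The number affected is unknown and probably below one. That rests on applying the 5% rate to this population, for which Section 8.5.6 gives neither dose nor exposure time, and on reading the tiers as bands. Sample size, power, error rate and analyses are untouched. The reason to amend is a possible serious harm and an avoidable ambiguity, not frequency.

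**What to change.** Rewrite the dose steps in Section 8.6.1 so that every case has one:

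- Factor 5 to below 10 with muscle symptoms: stop atorvastatin until CPK normalises and symptoms resolve.
- Factor 5 to below 10, no symptoms, normal CPK-MB: reduce to 20 mg.
- Factor 5 to below 10, no symptoms, raised CPK-MB: at least reduce to 20 mg while the source is worked up.
- Factor 10 or more: stop.

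The cost is a few amended lines and a letter to the sites. No new test is needed, since isoenzymes are already run above twice the upper normal range. The downside is slightly more atorvastatin interruption, probably in fewer than one patient. The analysis is unchanged: patients who stop medication are to be kept on the visit schedule (Section 7.1.3) and remain in the full analysis set (Section 11.1.2).

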### Elevated Transaminases/Leucocytes-count:

#### Patients with interferon-beta-1b monotherapy

1. leucocyte-count < 2500:
   - reduce dosage of interferon by 1/2 for 2 weeks
2. leucocyte-count < 2000:
   - stop interferon for 2 weeks
3. elevated tramsaminases times 3 of the upper value
   - reduce dosage of interferon by 1/2 for 2 weeks
4. elevated tramsaminases times 5 of the upper value
   - stop interferon for 2 weeks

After normalisation the therapy can be adapted

1. in case 1 and 3, the original dose can be administered
2. in case 2 and 4, interferon-beta-1b be must be slowly elevated

- ¼ of the final dosage for 1 week
- ½ of the final dosage for 1 week
- ¾ of the final dosage for 1 week
- full dose after 4 weeks

#### Patients with Interferon-beta-1b and Atorvastatin-therapy

- An elevation of the transaminases 3x the ULN can be tolerated.
- In case of an elevation of the transaminases the dose of Atorvastatin will be reduced first.

1. elevated tramsaminases ***times 3*** the ULN
   - halve the dosage of Atorvastatin (= 20 mg/d) for 2 weeks
2. elevated tramsaminases ***times 5*** the ULN
   - stop Atovastatin for 2 weeks

After normalisation the therapy can be adapted

- - in case 1 the original dose can be administered
  - in case 2 Atorvastatin will be administered 20 mg/d for 2 weeks and afterwards 40 mg/d

while increasing the dose, laboratory controls of the elevated values should be done every two weeks.

# Study Schedule

## Flow chart

The Table 1 provides a detailed schedule of activities and evaluations to be performed throughout the study.

**Table 1. Schedule of Activities and Evaluations**

| Activities and assessments | Baseline Day 1 | Month 3   telephone | Month 6 (+/- 7 days) | Month 9   telephone | Month 12 (+/- 7 days) |
| --- | --- | --- | --- | --- | --- |
| Written informed consent | ● |  |  |  |  |
| In-/exclusion criteria | ● |  |  |  |  |
| Demographic data | ● |  |  |  |  |
| MS history | ● |  |  |  |  |
| Medical/surgical history | ● |  |  |  |  |
| Physical examination | ● |  | ● |  | ● |
| Medication history | ● |  |  |  |  |
| Lab evaluation | 1,2 |  | 1 |  | 1,2 |
| Pregnancy test | ● |  |  |  |  |
| Urinalysis | ● |  |  |  | ● |
| Vital signs | ● |  | ● |  | ● |
| ECG | ● |  |  |  | ● |
| EDSS scoring | ● |  |  |  | ● |
| MSFC scoring | ● |  |  |  | ● |
| MRI | ● |  |  |  | ● |
| Drug accountability |  |  | ● |  | ● |
| Concomitant medication | ● | ● | ● | ● | ● |
| Adverse events |  | ● | ● | ● | ● |

Lab evaluation (s. 8.2.2):

1. Serum Chemistry, Serum lipids, Hematology, Creatine phosphokinase, Thyroid Profile
2. Immunology (2 serum-probes):

- Neutralizing Antibodies (Nab), Anti-MOG-, anti-MBP-Antibodies

# Activities

## Baseline visit (Day 1 visit)

- **The Screening visit is the final visit (month 15) of the SWABIMS-Study !!!**
- Before continuing the medication in the SWABIMS Follow up Study, the patient must give his/her written informed consent to participate.

### Procedures at baseline:

- Demographic data
- Inclusion and exclusion criteria
- Medical and surgical history
- MS history
- Medication history
- The contraceptive method used will be recorded, and if applicable, the age at menopause. Patients of childbearing potential will be instructed to discontinue study medication if they become pregnant and immediately notify the treating physician.
- Informed consent signature
- Vital signs
- Neurological examination by Evaluating Physician: EDSS
- MSFC scoring by Evaluating Physician or study nurse
- Physical examination
- Laboratory evaluations (Serum Chemistry, Serum lipids, Hematology, Urinalysis, Creatine phosphokinase, Thyroid Profile, Immunology (2 serum-probes stocks): Neutralizing Antibodies (Nab), Anti-MOG-, anti-MBP-Antibodies
- Pregnancy Test in women
- ECG
- MRI scan

## Treatment phase

The treatment phase begins at the Baseline visit (visit month 15 of the SWABIMS-Study) and terminates at months 12 visit.

### Month 6 visit (+/- 7 days)

- Physical examination
- Vital signs
- Drug accountability
- Concomitant medication
- Adverse events
- Laboratory testing:
  1. Serum Chemistry, Serum lipids, Hematology, Creatine phosphokinase, Thyroid Profile

### Months 12 Visit (+/- 7 days)

- Physical examination
- Vital signs
- Drug accountability (The unused study medication and used medication bottles will be collected).
- Concomitant medication use
- Adverse events: The patients will be queried orally regarding any AE they have experienced since the previous visit.
- Laboratory testing: Serum Chemistry, Serum lipids, Hematology, Urinalysis, Creatine phosphokinase, Immunology (2 serum-probes stocks): Neutralizing Antibodies (Nab), Anti-MOG-, anti-MBP-Antibodies
- MRI scan
- Neurological examination by Evaluating Physician (EDSS and MSFC)
- ECG

### Months 3 and 9 Visits (+/- 7 days)

- The patient will be called in order to collect information regarding concomitant medication an adverse events.

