## Secondary endpoints

- Gd-enhancing lesion on T1-weighted images after 12 months of treatment
- Change of total T2 hyperintense lesion volume after 12 months of treatment (burden of disease, BOD)
- Clinical disease progression (EDSS, MSFC)
- Functional system scores (of EDSS and MSFC)
- Number of relapse-free patients after 12 months of treatment
- Relapse rate after 12 months of treatment
- Time to first relapse
- Cortical atrophy (changes in brain volume, changes in grey matter and white matter) after 12 months of treatment
- Sieric levels of antibodies against myelin oligodendrocyte glycoprotein (anti-MOG) and against myelin basic protein (anti-MBP)
- Sierial levels of neutralizing Antibodies (Nab)

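### No scheduled contact after baseline has a relapse item although three secondary endpoints count relapses, so capture rests mainly on unblinded patients reporting an attack themselves

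*Protocol*

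**What the plan says.** Protocol section 6.2 lists three secondary endpoints that depend on counting relapses: "Number of relapse-free patients after 12 months of treatment", "Relapse rate after 12 months of treatment" and "Time to first relapse".

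The schedule after baseline has four contacts. Table 1 (section 9.1) has no relapse row, and it places EDSS scoring at baseline and Month 12 only. The Month 3 and 9 telephone contacts are described in one sentence (section 10.2.3): "The patient will be called in order to collect information regarding concomitant medication an adverse events". The Month 6 list (10.2.1) has no relapse item and no EDSS. The Month 12 list (10.2.2) includes EDSS and MSFC and, for adverse events, states: "The patients will be queried orally regarding any AE they have experienced since the previous visit". It has no relapse item either.

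Relapse reporting appears as a listed activity only under Unscheduled Visits (10.2.4). The trigger there is that "the patient believes that they are having a relapse or if a patient should call the study center with complaint of a relapse". On blinding, section 7.2.4 states: "All patients and the treating physician will be aware whether Atorvastatin is added to the Interferon-beta-1b therapy or not".

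**The concern.** An endpoint that counts events needs a procedure that looks for them in the same way in every patient. Here the schedule leaves the first step to the patient. He or she must decide that a symptom is a relapse, and either have it at the time of a call or phone the centre. Patients know whether they take atorvastatin, so the threshold for reporting could differ between arms. Blinding of the examining physician protects the EDSS score once a patient attends for a suspected relapse; it does not protect the decision to report.

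Under section 11.1.4 a patient without a relapse by Month 12 is censored at Month 12 in the time-to-relapse summary. An attack that nobody recorded therefore counts as an event-free year, and the patient counts as relapse-free. This is a matter of data collection, so no analysis plan can repair it afterwards.

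**Working it through.** **Step 1: read each scheduled contact after baseline for a relapse item.**

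| Contact | Relapse item | EDSS | Adverse events | Concomitant medication |
|---|---|---|---|---|
| Month 3 (call) | no | no | yes | yes |
| Month 6 (visit) | no | no | yes | yes |
| Month 9 (call) | no | no | yes | yes |
| Month 12 (visit) | no | yes | yes | yes |

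Result: 0 of 4 contacts have a relapse item, and no EDSS is scheduled between baseline and Month 12.

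**Step 2: check whether indirect routes close the gap.**

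- *Adverse events.* The definition in section 8.5 is wide enough to cover a relapse. No passage says that such an entry must be assessed against the relapse definition in section 7.2.6.
- *Concomitant medication.* Steroid treatment could reveal a relapse, but section 7.2.6 leaves the decision to treat to the treating physician. An untreated attack leaves no such trace.
- *Physical examination.* Section 8.3.7 excepts MS-related neurological findings from what must be reported.
- *EDSS at Month 12.* The relapse definition requires objective impairment shown by functional system and EDSS scores. A score at Month 12 cannot confirm an attack that resolved earlier.

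These routes can surface a relapse, but none obliges anyone to classify it as one.

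**Step 3: illustrate the size.** The protocol states no relapse risk, reporting share or power for these endpoints, so there is no figure of its own to reproduce. The risks and shares below are assumptions. The planned enrolment of about 60, half on atorvastatin (section 7), gives 30 per arm. The two-sided 5% level and Fisher's exact test come from sections 11.1.1 and 11.1.4.

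Observed relapse-free proportion = 1 − (true risk) × (1 − unreported share). With a true risk of 30% in both arms:

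- 20% unreported in both arms: 1 − 0.30 × 0.80 = 76%, against a true 70%.
- 10% unreported in one arm: 1 − 0.30 × 0.90 = 73%.
- 30% unreported in the other arm: 1 − 0.30 × 0.70 = 79%.

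The last two together make a spurious difference of 6 points, or 0.06 × 30 = 1.8 patients.

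The probability that Fisher's test rejects when the true risk is equal in both arms, by exact binomial enumeration with 30 per arm, is:

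| True risk | Full capture in both | 70% vs 90% captured | 50% vs 90% captured |
|---|---|---|---|
| 20% | 2.2% | 2.9% | 6.3% |
| 30% | 2.6% | 4.65% | 12.7% |
| 40% | 2.6% | 6.0% | 19.8% |
| 50% | 2.7% | 7.6% | 27.2% |

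The apparent risk ratio is 0.70/0.90 = 0.78 in the third column and 0.50/0.90 = 0.56 in the fourth, where the truth is 1.

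Equal but incomplete capture costs power. For a true relapse risk of 40% against 20%, Fisher power falls from 29.8% at full capture to 17.2% at 70% capture in both arms.

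**The case against.** The strongest reply is that relapses are not ignored. Adverse events and concomitant medication are asked at all four contacts, and Month 12 has an explicit oral query. Section 10.2.4 names the centre's own call as a moment when a relapse may come to light ("If during the center-initiated telephone call to the patient the patient believes that they are having a relapse"), and the phone-in route is open all year. The call script and case report form are not in the documents and may contain a relapse prompt. All of this stands. A reader might infer that a past attack is sought nowhere; that goes too far. What remains is that the protocol requires no such prompt and no check of suggestive entries.

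A reader might also infer that the blinded rater sees only patients who have already reported an attack. That is true of interim relapse assessment only, because EDSS is scored in every patient at baseline and Month 12.

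Nor would a question recover every missed event. An attack that has resolved can generally no longer meet the objective criterion in section 7.2.6. The gain lies in ongoing symptoms that the patient has not recognised as a relapse, in equal wording across arms, and in making the number of unconfirmed episodes visible.

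Finally, the reach is limited. The primary endpoint is read on MRI by blinded readers. Among the relapse endpoints, section 11.1.4 states a test only for the relapse-free proportion, and time to first relapse is summarised by a Kaplan-Meier plot.

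**Conclusion.** The point holds as a weakness in how secondary endpoints are ascertained. Three of them count relapses, no scheduled contact asks about relapse, and the only recording route depends on patients who know their arm. Relapses may be under-ascertained, possibly differently by arm.

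It would be tempting to state that relapses are under-counted, or that the comparison favours one arm. The documents support neither: reporting behaviour is unknown and bias could run either way. With a true risk of 30% and 10% against 30% unreported, both assumed, the estimate shifts by 6 points while the Fisher rejection rate is 4.65%, still below the nominal 5%. At modest differences in reporting the harm is thus mainly a biased estimate and lost events. Marked inflation of the false-positive rate needs a wide gap such as 50% against 90% capture. The primary endpoint is unaffected.

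**What to change.** Add a relapse assessment row to Table 1. In sections 10.2.1 to 10.2.3, add one question, worded identically in both arms, at Months 3, 6, 9 and 12. It should ask about any new or returning neurological symptom lasting more than 24 hours since the last contact, with onset date. Route ongoing symptoms to the existing unscheduled visit, and state there that EDSS is scored by the blinded examining physician; section 10.2.4 does not say who scores it. Require adverse event and steroid entries that suggest a relapse to be checked against section 7.2.6. Record episodes found too late to examine as unconfirmed, and report them by arm as a sensitivity analysis of the relapse endpoints.

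The cost is a short addition to the call script and case report form at contacts that already take place. The downside is some unconfirmed episodes that stay outside the main relapse counts.
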